### Data source

Data from RACF files has been accessed by site co-ordinators using a centralized database administered by the aged care provider. This database contains information recorded during routine clinical care and no assessment of residents will be undertaken outside of that required for usual care. Enrolment of participants occurred over a 12-month period during the pre-implementation and training phase of the IMPETUS-D project from December 2018, to December 2019, with baseline data and prognostic indicator variables collected at the time of enrolment. Mortality data will be collected until December 2020 and recorded at 6- and 12-month intervals post-assessment of prognostic indicator variables (*t*0). All study data will be recorded using the Research Electronic Data Capture tool (REDCAP) [18] in a secure online database administered by the University of Melbourne, Australia. The research database can only be accessed by research staff working on the project and all records will be stored for a minimum of 5 years after study completion.

### Participants

The cohort will comprise a minimum of 900 residents with dementia. Only residents who have been admitted to the RACF for a period of at least 90 days prior to enrolment will be eligible for inclusion if they have a documented diagnosis of dementia based on ICD-10 dementia definitions. Evidence of moderate to severe dementia will be required for study inclusion based on the cognitive skills assessment contained within the Aged Care Funding Instrument (ACFI) and dementia FAST staging.

The ACFI is a mandatory assessment instrument used to determine care needs and funding allocation for all residents of RACFs in Australia. Cognitive skills within the ACFI are divided into four groups (A, B, C, D) based on increasing degree of impairment such that group A has minimal impairment and group D has the most severe level of impairment. People with dementia with cognitive skills classified as group C or D (moderate to severe cognitive impairment) will be eligible for inclusion in the study. ACFI assessment of cognition uses the Psychogeriatric Assessment Scales—Cognitive Impairment Scale (PAS-CIS). This scale has been demonstrated to correlate well with the Mini-Mental State Examination (*r* = −0.77) [19] with higher scores indicating more severe impairment. Those with a PAS-CIS score of 10-15 are classified as cognitive skills C and those with a score of 16 or above as cognitive skills D. If the PAS-CIS score is not complete, the resident will be included if the ACFI appraisal determines that the resident meets the criteria to be classified as cognitive skills C or D based on evidence that they need assistance with the performance of activities of daily living due to cognitive impairment. In addition to ACFI criteria, study participants will need to meet the criteria for FAST stage 6e dementia at study entry. FAST staging correlates well with the trajectory of cognitive decline in moderate to advanced stages of dementia [20, 21] and stage 6e has been chosen as it represents the threshold for transition to the most advanced stage of dementia (FAST stage 7) for whom prognostic information may be particularly clinically relevant.

Baseline data collected will also include comorbid health conditions identified from diagnoses listed in RACF files matched to ICD-10 codes. Comorbidities will be clustered for analysis into the following groups: chronic lower respiratory diseases (J40-J47), chronic heart failure and cardiomyopathy (I11.0, I42, I50), chronic renal failure (N18-19), chronic liver disease (K70-K74), malignant neoplasms (C00-C97), and ischemic or hemorrhagic stroke (I60-I64).

The evolving Covid-19 (SARS-COV-2) pandemic [22] appears likely to impact RACFs in Australia during follow-up. Given the high mortality rate for Covid-19 among older adults and the unprecedented nature of the pandemic [23], participants who contract Covid-19 during follow-up will be excluded from the model development cohort.

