## Objectives

This study will aim to develop a prediction model for 6- and 12-month mortality for RACF residents with dementia using prognostic indicators recorded during routine clinical care. The model is intended to be applicable to people with dementia who have been living in a RACF for at least 3 months and to be utilized from 3 months onwards during the RACF admission.

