### Outcomes

Mortality data will be collected prospectively through a review of RACF files to identify all residents who died during the follow-up period. For any study participants who leave the RACF prior to 12 months of follow-up mortality information will be requested from the Department of Births Deaths and Marriages. Mortality will be divided for analysis into those that occurred within 6 months of study entry and those that occurred within 12 months of study entry. These mortality end points were chosen as they were considered most clinically meaningful. Estimation of the likelihood of death within 6 months is required for hospice eligibility in the USA [24] and is the end point for which the ADEPT model was developed. The Australian Commission on Safety and Quality in Healthcare focuses on those who are “likely to die within the next 12 months” in guidelines regarding end of life care [25] and whether a clinician would be surprised by death within 12 months (“the surprise question”) is often used for end of life identification [26].

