### Statistical analysis

Multivariable logistic regression will be used for model development rather than time-to-event methods such as the cox proportional hazards model. We expect to have complete outcome data for all participants at 12 months and have chosen the end points of 6- and 12-months for model development as these have particular clinical relevance. Using logistic regression to model these outcomes does not require an assumption of proportional hazards that may not apply to the prognostic indicators included in the model. The model will be developed through backwards elimination with a nominal level of alpha for variable exclusion set at 0.1 (10%). Using overly stringent levels of alpha for backwards elimination such as 0.05 is more likely to create an overly simplified model that eliminates relevant prognostic variables [48]. Non-linearity of continuous variables will be addressed by using a multivariable fractional polynomial approach, an established technique for transforming non-linear continuous variables when developing a backwards elimination model [49, 50]. The effect of exposure to the IMPETUS-D palliative care education intervention will be analyzed as an additional variable in multivariable analysis to assess whether the intervention influenced mortality. This approach does not require exclusion of those who received the intervention from model development reducing the potential for over-fitting of the model which is more likely to occur if model development is limited to the control group only [51]. A sensitivity analysis of model performance in both the intervention and control groups will also be undertaken.

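### Excluding anyone infected with Covid-19 at any point in follow-up removes known survivors from the 6-month model and raises its estimated risk; the exclusion should be defined separately for each endpoint

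*Protocol article*

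**What the plan says.** The Participants section expects that the pandemic "appears likely to impact RACFs in Australia during follow-up" and gives its reason for acting: "Given the high mortality rate for Covid-19 among older adults and the unprecedented nature of the pandemic". The rule that follows is that "participants who contract Covid-19 during follow-up will be excluded from the model development cohort". It refers to a single development cohort and sets no time limit on infection relative to either endpoint.

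The Outcomes section divides deaths into "those that occurred within 6 months of study entry and those that occurred within 12 months of study entry". The Statistical analysis section models both as binary outcomes by logistic regression, so a resident is either wholly in or wholly out of a model.

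Under Data source, enrolment ran "from December 2018, to December 2019, with baseline data and prognostic indicator variables collected at the time of enrolment", and "Mortality data will be collected until December 2020". Six-month windows therefore close between about June 2019 and June 2020, while follow-up continues to the end of 2020. The Objectives intend the model "to be utilized from 3 months onwards during the RACF admission".

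The sensitivity analyses described (complete cases under Missing data, trial arm under Statistical analysis) do not address the Covid-19 exclusion.

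**The concern.** The rule selects residents on something that happens after baseline and that requires being alive. Residents who die early cannot later be infected, so they always stay in. Those removed are survivors to their infection date. For the 6-month model this is clearest: anyone infected after month 6 is a known survivor with a settled outcome, and the stated reason, high Covid-19 mortality, gives no ground for discarding that outcome.

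The model's product is an absolute risk for a resident whose future infection status is unknown, so the selection cannot be reproduced at the point of use. The planned calibration plots and bootstrap correction are computed within the selected cohort and cannot reveal the shift.

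**Working it through.** **Inputs from the protocol.** Minimum cohort 900 (Participants); 12-month mortality 30%, 200 deaths required, 10 predictors (Sample size); enrolment December 2018 to December 2019 (Data source).

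**Assumptions not in the protocol.** Constant hazard; uniform entry over 12 months; Covid-19 starting in January or March 2020; 2% to 20% of the cohort infected within 12 months of t0; fatality 10% to 50%, with death one month after infection.

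**The plan's own figures.** 10 × 20 / 0.30 = 666.7, rounded up to 667. The shrinkage criterion gives 10 / [(0.9 − 1) × ln(1 − 0.208/0.9)] = 380.5, rounded up to 381, and 381 × 0.3 / 10 = 11.43 events per variable. Both reproduce.

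**Step 1: 6-month risk, closed form.** With 30% at 12 months, 6-month risk is d = 1 − 0.7^0.5 = 16.3%, or 147 deaths and 753 survivors among 900. If a share q of the survivors is dropped for later infection, risk becomes d / [d + (1 − d)(1 − q)]. The odds are divided by (1 − q), so the log-odds rise by −ln(1 − q).

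- q = 5%: about 38 residents dropped; 147 / (147 + 715.3) = 17.0%; log-odds +0.051.
- q = 10%: about 75 dropped; 147 / (147 + 677.7) = 17.8%; log-odds +0.105.
- q = 20%: about 151 dropped; 147 / (147 + 602.4) = 19.6%; log-odds +0.223.

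The direction needs no assumption about when the pandemic began or how lethal it was.

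**Step 2: staggered entry.** A simulation of 1,000,000 residents, with infection possible only while alive, has Covid-free risks of 16.37% at 6 months and 30.0% at 12 months. Each cell gives January / March 2020 start.

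| Cohort infected | 6-month risk, protocol rule | 6-month risk, only infections before month 6 excluded | 12-month risk, protocol rule |
|---|---|---|---|
| 2% | 16.68 / 16.69% | 16.42 / 16.40% | 30.40 / 30.43% |
| 5% | 17.17 / 17.21% | 16.51 / 16.46% | 31.00 / 31.12% |
| 10% | 18.05 / 18.14% | 16.65 / 16.55% | 32.13 / 32.33% |
| 20% | 20.13 / 20.34% | 16.99 / 16.77% | 34.74 / 35.18% |

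Between 74% and 77% of infections (January start) or 85% and 87% (March start) fall after month 6. The share of 6-month windows already closed when Covid-19 starts is (13 − 6)/12 = 58% or (15 − 6)/12 = 75%. Most excluded residents therefore have a 6-month outcome that Covid-19 never touched.

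**Step 3: why 12-month risk rises against Covid-free mortality.** Having survived to infection, the excluded residents have a Covid-free 12-month risk of only about 9% to 11%. Removing a fraction p with risk r gives (0.30 − p·r)/(1 − p). For a March start, p = 5% and r = 8.7% give (0.30 − 0.00435)/0.95 = 31.1%; p = 20% and r = 9.3% give (0.30 − 0.0186)/0.80 = 35.2%.

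**Step 4: against all-cause mortality.** At 5% infected, 12-month all-cause risk including Covid-19 deaths is about 30.4%, 31.1% and 31.8% for fatality of 10%, 30% and 50%. The protocol rule gives 31.0% to 31.1%, so the sign of the difference changes at a fatality of about 30%.

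**Step 5: events.** Of 900 residents, the retained cohort still has about 250 to 268 deaths by 12 months, above the 200 required.

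**The case against.** The strongest defence is that the exclusion is deliberate. The authors want a model of mortality outside an unprecedented pandemic, and counting Covid-19 deaths would distort it. That is a legitimate target and a fair reason to treat infections before an endpoint specially. It does not reach infections after the endpoint, which cannot have affected the outcome.

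A second defence is that little harm follows. With one normal predictor, a c statistic of about 0.70, and infection independent of the predictor given survival, excluding 10% of those alive at month 8 moves the 6-month slope from 0.740 to 0.735 and c from 0.691 to 0.690. The 12-month slope goes from 0.812 to 0.814 and c from 0.703 to 0.704. With 30% excluded, c moves by at most 0.004. The Discussion also calls the model preliminary and requires external validation first. This stands: the damage is mainly to the intercept and calibration, though it could be wider if infection depends on the predictors.

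Some stronger readings are tempting but not supported:

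- That risk is inflated at both horizons whatever the target. At 12 months this holds only against Covid-free mortality (step 4).
- That the error could be as large as a single month-8 outbreak suggests. Excluding 30% of everyone alive at month 8 would give 21.4% at 6 months and 35.8% at 12 months, but it removes 23.6% of the cohort and puts every resident at the same follow-up time, which the year-long enrolment rules out.
- That the expectation "We expect to have complete outcome data for all participants at 12 months" contradicts the exclusion. It concerns knowledge of vital status and neither conflicts with the rule nor aggravates it.
- That between-facility comparisons are shown to be distorted. This is plausible if infections cluster by facility, but the protocol gives nothing from which to size it.

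**Conclusion.** The concern holds. For infections after month 6, the upward shift in 6-month risk is certain in direction, and discarding those outcomes serves no purpose that the protocol states. At 12 months the rule raises risk relative to Covid-free mortality, the target implied by its rationale; no direction can be claimed relative to all-cause mortality without knowing Covid-19 fatality.

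The size is unknown because the protocol gives no infection rate. Under the assumptions above, it is 0.3 to 0.4 percentage points at 2% infected and about 4 to 5 points at 20%, counting both horizons. With very few infections it would be negligible. Discrimination and the number of events are not materially at risk. The point warrants correction because the model's purpose is to state absolute risk.

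**What to change.** Define the exclusion separately for each endpoint. No participant should be dropped from the 6-month model for an infection after their own 6-month date, or from the 12-month model for an infection after their own 12-month date. Report a sensitivity analysis for both models that keeps all residents and counts every death, and state whether the primary target is Covid-free or all-cause mortality.

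Censoring at the infection date with inverse-probability weights is an option if infections prove numerous. It need not be required: the weights would have to be carried through multiple imputation, fractional-polynomial elimination and 400 bootstrap repeats, and could be unstable with few, clustered infections.

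The cost is an infection date for each case and slightly different cohorts for the two models. A small residual bias remains, because infections before an endpoint also require survival to infection: in the simulation, 6-month risk is 16.77% to 16.99% against 16.37% at 20% infected. The all-residents analysis would help to gauge it.

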### Outcomes

Mortality data will be collected prospectively through a review of RACF files to identify all residents who died during the follow-up period. For any study participants who leave the RACF prior to 12 months of follow-up mortality information will be requested from the Department of Births Deaths and Marriages. Mortality will be divided for analysis into those that occurred within 6 months of study entry and those that occurred within 12 months of study entry. These mortality end points were chosen as they were considered most clinically meaningful. Estimation of the likelihood of death within 6 months is required for hospice eligibility in the USA [24] and is the end point for which the ADEPT model was developed. The Australian Commission on Safety and Quality in Healthcare focuses on those who are “likely to die within the next 12 months” in guidelines regarding end of life care [25] and whether a clinician would be surprised by death within 12 months (“the surprise question”) is often used for end of life identification [26].

### Candidate predictor variables

The prognostic indicators for consideration in the multivariable model were identified from a literature review (unpublished) examining clinical features associated with increased mortality for people with dementia (see Table 1). Given the aim is to create a model that could be readily incorporated into routine clinical care, a parsimonious approach was taken to a selection of prognostic indicators with ten variables selected that could be easily assessed by RACF staff through a brief audit of the patient record. The number of variables chosen was also informed by consideration of the minimum number of events per variable required for model development (see sample size below).

**Table 1 Tab1:** Candidate predictor variables

At study entry	Prior to study entry
Age [27]	Pressure injuries within the last 3 months [28, 29]
Sex [27]	Weight loss over the last 6 months [30]
Level of support required for oral intake [31]	Infections in the last 3 months [29]
Level of support required to transfer out of bed [31]	Hospital admissions in the last 3 months [32]
BMI [33]	Number of falls in the last 3 months [34]

Pressure injuries, infections, falls, and hospital admissions are recorded through mandatory clinical documentation during routine care at the participating RACF sites. The frequency of these clinical episodes will be assessed for 3 months prior to study entry. More than 10% weight loss in 6 months has been identified as a predictor of mortality in previous studies and thus a 6-month period was chosen for calculation of percentage weight loss [10, 30].

The level of staff assistance for oral intake and transferring out of bed will be assessed from care documented in RACF files and quantified using descriptors from the Minimum Data Set ADL Scale (MDS ADL). The MDS ADL scale has been validated against other functional assessment scales in long-term care [35] and is able to detect change in function for people with cognitive impairment living in RACFs [36]. A decline in MDS ADL scale scores for oral intake and transferring ability, in particular, occurs more commonly in the last months of life for people with advanced dementia [31]. The MDS ADL scale divides the level of assistance required to complete a task into five categories of increasing dependence. A score of zero is given for independence, increasing to a score of four for total dependence on staff to complete the activity.

### Sample size

The study cohort will be derived from 24 RACFs comprising a minimum of 2400 residents receiving long-term care. Assuming that 50% of residents will have a diagnosis of dementia based on previous published data from long-term care in Australia [37], there will be an estimated minimum of 1200 residents with dementia. Three quarters (77.3%) of people with dementia in RACFs in Australia have moderate to severe cognitive impairment [38] equating to a minimum of 900 people with dementia who would meet the criteria for inclusion in the cohort.

A minimum of 10 events per variable has been proposed as a reasonable sample size for the development of predictive models [39] and increasing the sample size to 20 events per variable appears to improve the reliability of results [40]. For the ten prognostic indicator variables, a minimum of 200 events (deaths) are therefore required to reach a minimum of 20 events per variable. In RACFs in Australia, the 12-month mortality rate for people with dementia is approximately 30% [37], which is similar to mortality rates found in cohort studies of people with dementia in long-term care in the USA [41, 42]. Assuming a mortality rate of 30%, the required minimum cohort size for the model development cohort is therefore 667 people with dementia to observe a minimum of 200 deaths.

An alternative method for estimating the minimum sample size required for model development has been recently proposed by Riley et al. [43]. Using the optimism corrected c statistic for 12-month mortality reported for the ADEPT model (*c* = 0.68) [42], a *R*^2^_D_ value of 0.208 can be derived. This value can then be used to estimate sample size when combined with a prespecified level of shrinkage for the final model along with the expected event rate and the number of candidate predictor variables. Using the pmsampsize package in R version 3.6.2 with an *R*^2^ of 0.208, shrinkage factor of 0.9, event rate of 0.3, and 10 predictor variables gives a minimum sample size of 381 with 11.43 events per variable. The estimated minimum study cohort of 900 people will therefore exceed this figure and also the more conservative 20 events per variable estimate.

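### The stated minimum of 900 eligible residents leaves out two inclusion criteria, FAST stage 6e and the 90-day stay, so it is a count before screening

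*Protocol article*

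**What the plan says.** The Sample size section of the protocol article builds the cohort in three steps. It starts from "24 RACFs comprising a minimum of 2400 residents receiving long-term care". It then halves that number: "Assuming that 50% of residents will have a diagnosis of dementia", which gives 1200. The last step uses a published severity share, "Three quarters (77.3%) of people with dementia in RACFs in Australia have moderate to severe cognitive impairment", and ends with "equating to a minimum of 900 people with dementia who would meet the criteria for inclusion in the cohort".

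The Participants section repeats the number as a commitment: "The cohort will comprise a minimum of 900 residents with dementia". The same section sets the eligibility rules. Besides a documented dementia diagnosis and ACFI cognitive skills group C or D, there are two more:

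- FAST stage: "In addition to ACFI criteria, study participants will need to meet the criteria for FAST stage 6e dementia at study entry".
- Length of stay: "Only residents who have been admitted to the RACF for a period of at least 90 days prior to enrolment will be eligible".

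It also provides for a removal after entry: "participants who contract Covid-19 during follow-up will be excluded from the model development cohort".

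The Sample size section compares 900 with two requirements: 667 residents (200 deaths at 30% 12-month mortality, 20 per variable for ten variables) and 381 residents (shrinkage-based method). It concludes that 900 exceeds both.

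**The concern.** The calculation uses two proportions, dementia and moderate to severe impairment, yet presents the product as the number satisfying all the inclusion criteria. FAST 6e is expressly required on top of the ACFI criterion, and the 90-day rule is a separate condition. Each can only reduce the count. A number that precedes two eligibility screens cannot be the minimum that passes them unless the starting population is larger than stated or nearly everyone passes.

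The protocol's own description suggests that the FAST criterion may matter. It presents stage 6e as the point of transition to the most advanced stage, whereas ACFI C or D covers moderate as well as severe impairment. At stake is the claim that the cohort will clear the more conservative standard of 20 events per variable, because that claim is read directly off the 900.

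**Working it through.** **Inputs (protocol article, Sample size section):** 2400 residents; 50% with dementia; 77.3%, worded as three quarters, with moderate to severe impairment; 12-month mortality 30%; ten variables; targets of 667 and 381. The documents give no proportion for FAST 6e, for the 90-day stay or for Covid-19.

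**1. The plan's figure.**
- With three quarters: 2400 × 0.50 × 0.75 = 900.
- With 77.3%: 2400 × 0.50 × 0.773 = 927.6.

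The 900 reproduces exactly with the rounded share. The multiplication is right, and no factor for FAST 6e or the 90-day stay appears in it.

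**2. The targets.**
- 20 events per variable: 200 / 0.30 = 666.7, rounded up to 667.
- Shrinkage method with the protocol's inputs: 10 / [(0.9 − 1) × ln(1 − 0.208/0.9)] = 380.5, rounded up to 381. I take those inputs as given here.
- Expected deaths at 900: 900 × 0.30 = 270, or 27 per variable.

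**3. Slack at the stated base.** 900 / 927.6 = 97.0%. If more than 3.0% of the 927.6 fail FAST 6e or the 90-day rule, fewer than 900 are eligible.

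**4. Break-even fractions.** Let q be the share that remains after the omitted reductions.

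| Target | q from 900 | q from 927.6 |
|---|---|---|
| 667 | 667/900 = 74.1% | 667/927.6 = 71.9% |
| 381 | 381/900 = 42.3% | 381/927.6 = 41.1% |

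**5. Range for q (assumed values, starting from 900, 30% mortality).**

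| q | Residents | Deaths | Events per variable |
|---|---|---|---|
| 0.9 | 810 | 243 | 24.3 |
| 0.8 | 720 | 216 | 21.6 |
| 0.7 | 630 | 189 | 18.9 |
| 0.6 | 540 | 162 | 16.2 |
| 0.5 | 450 | 135 | 13.5 |
| 0.4 | 360 | 108 | 10.8 |

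**6. Sensitivity to mortality (assumed).** The 30% refers to people with dementia in aged care generally. If it were 40% in a FAST 6e cohort, 200 deaths would need 200/0.40 = 500 residents, and the break-even would fall to 500/900 = 55.6%.

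**7. Base needed to keep 900 eligible.** Residents = 900 / (0.50 × 0.773 × q). This gives about 2,587 at q = 0.9, 2,911 at q = 0.8 and 3,327 at q = 0.7.

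**The case against.** Five points can be made for the protocol.

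- **The base of 2400 is itself a minimum.** This stands. A reader might infer that 900 is a ceiling, but it bounds the eligible number only if the facilities hold 2400 residents and no more. The Data source section also describes enrolment over 12 months, so turnover could add residents, while the Study design section ties data extraction to randomization. The documents leave this open. They do not claim the larger base that step 7 would require.
- **FAST 6e may overlap with the severity share.** The Participants section introduces ACFI and FAST together as evidence of moderate to severe dementia, so the loss could be small. This limits what can be said about size. It does not remove the omission, because FAST 6e is stated as an additional requirement.
- **The study may still be large enough.** This also stands. A reader might infer that every adequacy statement fails, but the 381 target survives the loss of more than half the 900, and the 10 events per variable that the protocol cites as reasonable needs only 100 deaths. Only the 20-per-variable claim is exposed, and higher mortality at FAST 6e could protect part of it.
- **Covid-19 is not an inclusion criterion.** Correct. It does not bear on how many meet the criteria at entry. It reduces the model development cohort afterwards, and that cohort is the one the 667 refers to.
- **An article condenses its source.** That would excuse a missing detail. Here a figure is printed and attributed to criteria that were not applied.

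**Conclusion.** The point holds for the derivation. At the stated base of 2400 residents, 900 (927.6 unrounded) is the number before FAST and length-of-stay screening, and the protocol is wrong to call it the minimum who meet the inclusion criteria. This conclusion needs no outside figure.

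The size of the shortfall cannot be determined from the documents. What can be stated is conditional: with 30% mortality, 20 events per variable is lost once fewer than about 74% of the 900 (72% of 927.6) remain, and 381 is lost only below about 42% of the 900 (41% of 927.6). A reader might go further and conclude that the study is underpowered or that a particular number of deaths will be missing. The documents do not support that: every value of q and any mortality other than 30% is an assumption, and the starting 2400 may be exceeded.

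**What to change.** In the Participants and Sample size sections, replace the minimum of 900 with the number actually enrolled. Enrolment ran to December 2019 with baseline data collected at enrolment, so that count should already be available to the sponsor, although the article does not give it. State separately how many are later removed for Covid-19, since this sets the size of the development cohort.

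If a projection is kept, label 900 as the number before FAST and length-of-stay screening, and multiply it by explicit, sourced fractions for FAST 6e and for the 90-day stay. In either case, restate expected 12-month deaths and events per variable, say whether 30% mortality is suitable for a FAST 6e cohort, and make the claim of exceeding 20 events per variable conditional on the resulting count. The comparison with 381 can be kept, shown against the same count.

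The cost is a few sentences and a count from the existing database. The design and the analysis do not change. The drawback is that the printed figures may become less favourable.

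### The stated minimum of 381 comes from entering R²_D as a Cox-Snell R²; the corrected minimum is about 830 to 1,020, so a comfortable margin at 900 is not supported

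*Protocol article*

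**What the plan says.** The Sample size section of the protocol article gives two justifications. The first is events per variable: ten variables at 20 events each need 200 deaths, which at 30% mortality means 667 people. The second uses recently proposed criteria for prediction-model sample size. It starts from a published model: "Using the optimism corrected c statistic for 12-month mortality reported for the ADEPT model", with c = 0.68. From this, an R²_D "value of 0.208 can be derived". That number is then entered as the R² in pmsampsize, and the outcome is reported as "of 0.208, shrinkage factor of 0.9, event rate of 0.3, and 10 predictor variables gives a minimum sample size of 381". The accompanying events-per-variable figure is given as 11.43.

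The section describes no step between R²_D and the R² that is entered. It concludes: "The estimated minimum study cohort of 900 people will therefore exceed this figure and also the more conservative 20 events per variable estimate". The Statistical analysis section fixes multivariable logistic regression, not a time-to-event model, as the method.

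**The concern.** R²_D measures explained variation on the scale of a survival model's linear predictor. The shrinkage criterion for a binary outcome is written in terms of the Cox-Snell R², which depends on the event rate and is much smaller for the same discrimination. Putting one in place of the other makes the anticipated model look far stronger than c = 0.68 implies, and a stronger anticipated model needs fewer people to reach the same shrinkage target.

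What is at stake is the planning claim. With 381 as the benchmark, a cohort of 900 appears to have more than twofold headroom against over-fitting (900/381 = 2.4), and the 20-events-per-variable rule appears to be the stricter of the two tests. If 381 is wrong, neither impression is safe.

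**Working it through.** **Inputs, all from the Sample size section:** c = 0.68; R²_D = 0.208; shrinkage target S = 0.9; event rate 0.3; P = 10; stated result 381 with 11.43 events per variable; planned minimum cohort 900; separate 20-events-per-variable figure 667.

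**1. Where 0.208 comes from.**
- D = 5.50(c − 0.5) + 10.26(c − 0.5)³ = 5.50(0.18) + 10.26(0.18)³ = 1.050
- R²_D = (π/8)D² / (π²/6 + (π/8)D²) = 0.433 / (1.645 + 0.433) = 0.208

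The π²/6 term is the survival-scale error variance, so 0.208 is R²_D, as the plan labels it.

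**2. Reproducing 381.** The shrinkage criterion is n = P / [(S − 1) ln(1 − R²_CS/S)], where R²_CS is the Cox-Snell R².
- With R²_CS = 0.208: n = 10 / [−0.1 × ln(1 − 0.208/0.9)] = 10 / (0.1 × 0.2628) = 380.5, rounded up to 381
- Events per variable: 381 × 0.3 / 10 = 11.43
- The other two criteria give 248 (optimism in R²) and 323 (precision of the overall risk), so shrinkage governs

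Both stated figures match exactly, so 0.208 was used as a Cox-Snell R².

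**3. Is 0.208 compatible with c = 0.68?** With a linear predictor that is normal within each outcome group and 30% events, a Cox-Snell R² of 0.208 corresponds to c of about 0.79. It is not compatible.

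**4. Corrected minimum, logistic route.** The Cox-Snell R² for c = 0.68 and 30% events, by numerical integration, is 0.0841 (predictor normal within outcome groups) or 0.0840 (predictor normal overall).
- n = 10 / [−0.1 × ln(1 − 0.0841/0.9)] = 1,020 (1,021 with 0.0840)
- 1,020 × 0.3 / 10 = 30.6 events per variable; 1,020/381 = 2.7
- For c = 0.685 the minimum is 964; for c = 0.675 it is 1,081

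**5. Corrected minimum, survival-scale route.** Here the plan's own R²_D is converted through the O'Quigley R².
- R²_OQ = (π²/6)(0.208) / [1 + (π²/6 − 1)(0.208)] = 0.302
- R²_CS = 1 − (1 − 0.302)^0.3 = 0.102
- n = 10 / [−0.1 × ln(1 − 0.102/0.9)] = 831 (using unrounded R²_CS = 0.1021)
- 831 × 0.3 / 10 = 24.9 events per variable; 831/381 = 2.2

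On both routes the other two criteria stay well below these values (at most 323).

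**6. Expected shrinkage with 10 parameters**, solving the same formula for S:

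| n | Logistic route | Survival-scale route |
|---|---|---|
| 381 | 0.772 | 0.806 |
| 667 | 0.855 | 0.879 |
| 900 | 0.888 | 0.907 |

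**7. Sensitivity to the parameter count.** The minimum is proportional to P. The Statistical analysis section adds intervention exposure as a further variable. If that counts as an eleventh parameter, the minima become 1,019.8 × 1.1 = 1,122 and 830.3 × 1.1 = 914 (rounded up), both above 900. Fractional polynomial terms would add to P again.

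**The case against.** A reader might infer that the plan's sentence about 900 is false. It is not. It compares 900 with 381 and with 667, and both comparisons are arithmetically true. The first benchmark is invalid; the comparison with 667 is unaffected and should stay.

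A reader might also infer that 900 definitely misses the target and that 1,020 is the one correct figure. The documents do not support that. They do not say what kind of model or c statistic produced 0.68, and converting the plan's own R²_D on the survival scale gives about 830, which 900 exceeds. Even on the logistic route the shortfall is small (0.888 against 0.90). Moreover, 900 is a floor: 2,400 × 0.50 × 0.773 = 928, where shrinkage is 0.891. The result is also sensitive to c, since at c = 0.69 the logistic minimum falls to 912. These points stand, and they limit the claim about 900. They do not rescue 381, which is far too small on either route.

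Finally, it can be said that little depends on this figure. The calculation is presented as an alternative to the events-per-variable argument, enrolment ended in December 2019, the model-building process is to be repeated in 400 bootstrap samples to obtain optimism-adjusted slopes and c statistics, and the Discussion calls the model preliminary. This is fair. Over-fitting will be measured whatever was entered in the software, so the error affects the planning justification and not the validity of the analysis.

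**Conclusion.** The concern holds as an error in a stated figure. R²_D was entered where a Cox-Snell R² is required, and 381 with 11.43 events per variable is wrong. The corrected minimum is about 1,020 (about 31 events per variable) by the logistic conversion, which best matches the planned model, or about 830 (about 25) by the survival-scale conversion: 2.2 to 2.7 times the stated figure. A cohort of 900 falls short on the first route and just passes on the second, so the comfortable margin is not supported. On either route 667 lies below the corrected minimum, so the 20-events-per-variable rule is no longer the more conservative test.

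These figures take the plan's c = 0.68, 30% 12-month mortality, S = 0.9 and exactly 10 parameters as given. The logistic route also assumes an approximately normal linear predictor; the two forms tried agree to within one person.

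**What to change.** In the Sample size section:
- Redo the calculation with a Cox-Snell R², and state how it was obtained from c = 0.68 and how many candidate parameters were counted.
- Replace 381 and 11.43 with the corrected figures: about 1,020 and 31 by the logistic conversion, or about 830 and 25 if the survival-scale conversion is chosen and justified, both for 10 parameters.
- Replace the claim that 900 exceeds this minimum with the expected shrinkage at the actual sample size. Keep the comparison of 900 with 667.
- Drop the description of the 20-events-per-variable figure as the more conservative one.

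The cost is one reworded paragraph and a less favourable figure; no extra participants are needed. Multiplying the final coefficients by the bootstrap-estimated slope and re-estimating the intercept would be a sensible optional addition, since that slope is already to be estimated, but the correction does not depend on it.
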